## Abstract

**Background:**

Functional endoscopic sinus surgery is a principal option for treating chronic rhinosinusitis with nasal polyps (CRSwNP) after medication failures. Unfortunately, some patients still have unsatisfactory postoperative recovery. The type of inflammatory cell infiltration in nasal polyp tissue has been reported available for recurrence prediction. As it is invasive and time-consuming, this technique is hard to promote clinically under the existing technical conditions. And during the course of clinical treatment, we have noted that differences in the postoperative recurrence rate of patients present among different traditional Chinese medicine syndrome types.

**Methods and analysis:**

This is a non-randomized, single-center, and prospective cohort study started in Chengdu Sichuan Province, People’s Republic of China, in January 2021. A total of 200 participants will be recruited from patients who are diagnosed with CRSwNP and prepared for functional endoscopic sinus surgery. We collect preoperative data which includes general information, medical history, TCM syndromes, visual analogue scale (VAS) of subjective symptoms, Lund-Kennedy endoscopic score, and Lund-Mackay score of computed tomography (CT) scanning of sinuses. We acquire the VAS score and Lund-Kennedy score of subjective symptoms through multiple planned follow-up after surgery. After 1 year of follow-up, the recurrence rate will be calculated, and the curative effect will be assessed. Meanwhile, the patients’ pathological sections will be sorted out, and inflammatory cell infiltration will be analyzed. Statistical analysis will be carried out to evaluate the correlation among CRSwNP recurrence and TCM syndrome types and tissue inflammatory cell infiltration types. Then we will establish a predictive model for CRSwNP recurrence. Analyses of survey data include descriptive and inferential statistical approaches.

**Discussion:**

This is the first prospective cohort study on investigating the correlation of CRSwNP recurrence with TCM syndrome types and tissue inflammatory cell infiltration types. Through this study, we hope to discover a new and simple, effective, and noninvasive way to predict the recurrence rate rapidly after CRSwNP and provide reference for the intervention timing of traditional Chinese medicine application, thereby achieving customized diagnosis and treatment, minimizing risks of surgical events, and delaying postoperative recurrence of CRSwNP.

**Systematic review registration:**

PROSPERO ChiCTR2100041646.

## Background

Chronic rhinosinusitis with nasal polyps (CRSwNP) refers to the chronic inflammation of the sinuses and nasal mucosa, accompanied by nasal polyps. The course of the disease exceeds 12 weeks. The clinical symptoms include nasal congestion, purulent nasal discharge, sense of smell disorders, headache, and intranasal polyps [1, 2]. Functional endoscopic sinus surgery (FESS) is the major method for clinical treatment of CRSwNP when maximal drug therapy fails [3]. With the extensive development of FESS and the gradual maturity of technology and equipment, the clinical cure rate of CRSwNP has gradually improved. Despite this, there are still about 30 to 60% of patients who complain about the unsatisfactory post-surgery recovery, residual nasal discharge, and no recovery of smell. Relevant studies by DeConde A. S. have found that the recurrence rate of CRSwNP is as high as 40% at 18 months after surgery [4]. A 2-year follow-up of CRSwNP in the Chinese population has indicated the recurrence rate of 55.6% [5].

Several recent studies have shown an intimate association between the type of inflammatory cell infiltration in nasal mucosal polyps and postoperative recurrence [6–8]. The intrinsic pathological features of eosinophilic and non-eosinophilic nasal polyps affect greatly on surgical effect and post-surgery recurrence [7, 9]. Wang et al. have reported that the accuracy of eosinophil (EOS) in predicting post-surgery recurrence can be as high as 90% [7]. This is helpful for both surgeons and patients to have a more accurate judgment for the results of surgery, and corresponding individualized management plans can be designed as per the prognosis, laying a foundation for the realization of CRSwNP precise treatment. However, sufficient polyp tissues are hard to be collected when the patient is conscious, plus cell counting is time-consuming; it is therefore difficult to promote extensive clinical application under current conditions.

There is a concept of “syndrome” in traditional Chinese medicine (TCM), known as “ZHENG,” which is an important part of the theory of TCM [10, 11]. Syndrome differentiation is one of the most important concepts in the practice of TCM and comprises a series of diagnostic procedures. Syndrome differentiation is the process of comprehensive analysis of clinical information obtained by the four main diagnostic TCM procedures: observation, listening, questioning, and pulse analyses [12].

The information obtained from traditional Chinese medicine syndrome differentiation includes symptoms, pulse patterns, and tongue patterns, which are considered subjective. However, compared to other prediction tools, traditional Chinese medicine syndrome has advantages because it does not require complex and time-consuming laboratory test for clinical prognosis or survival prediction. Scholars have found that the differentiation and classification of traditional Chinese medicine syndromes have certain significance in predicting the survival of advanced cancer patients [13]. The prognosis of primary liver cancer patients with syndrome of liver depression and spleen deficiency is the best, while the prognosis of syndrome of yin deficiency in the liver and kidney is bad [14].

Based on the main symptoms, accompanied symptoms, tongue and pulse conditions, and local examination characteristics of patients in traditional Chinese medicine, the *Otorhinolaryngology of TCM* classifies the disease into four traditional Chinese medicine (TCM) syndrome types: damp heat in the spleen and stomach, stagnant heat in gallbladder, deficiency and weak in spleen qi, and deficiency and cold in lung qi under the principles of *Otorhinolaryngology in Traditional Chinese Medicine*. In the course of clinical treatment, we have noted that the recurrence rate of patients with different TCM syndromes varies to some extent [15–18]. Previous research have indicated that the 1-year postoperative recurrence rate in patients with the types of deficiency and weak in spleen qi, and deficiency and cold in lung qi, is higher than that of patients with damp heat in the spleen and stomach and stagnant heat in gallbladder [17, 18]. After FESS surgery, although there are many factors that affect the prognosis, such as the exposure stage after discharge, living and dietary environment, and the patient's selfdiscipline. It is certain that the postoperative recurrence rate of the first two TCM syndromes is markedly higher than that of the latter two types, which occurs not an isolated case but according to some regular rules.

Since both TCM syndromes and tissue inflammatory cell infiltration are associated with the recurrence rate of CRSwNP, do the characteristics of tissue inflammatory cell infiltration correlate with TCM syndrome types? That is, there are differences in the inflammatory cell infiltration of CRSwNP in different TCM syndrome types, and this difference is a key factor influencing the postoperative recovery of CRSwNP. Hence, we designed a non-randomized, single-center prospective cohort study to explore the correlation among the recurrence rate of CRSwNP and TCM syndrome types and the characteristics of tissue inflammatory cell infiltration. Through this study, we hope to discover a new and simple, effective, and noninvasive way to predict the recurrence rate rapidly after CRSwNP and provide a direction for thinking about the timing of intervention in traditional Chinese medicine, thereby achieving customized diagnosis and treatment, minimizing risks of surgical events, and delaying postoperative recurrence of CRSwNP.

## Methods/design

### Design overview

This study is a non-randomized, single-center, prospective cohort study, starting in January 2021, and it is currently ongoing. A total of 200 patients at 12–75 years of age who are prepared to undergo FESS will be recruited from Hospital of Chengdu University of Traditional Chinese Medicine.

Due to the similar degree of improvement in endoscopic scores and quality-of-life indicators among patients undergoing chronic sinusitis surgery at different age groups, or without exceeding the minimum clinically important differences [19–21], this study did not consider further age stratification factors. All participants are diagnosed with CRSwNP. And preoperative data will be collected, as well as follow-up visits and relevant data collection after surgery. All participants should be advised to undergo regular follow-up examinations and treatments at the hospital after surgery, regardless of their participation in our study. We are simply following up on patients.

The participants will be scheduled with follow-up at 2 weeks, 4 weeks, and 2, 3, 6, 9, and 12 months after surgery. The included patients will be assigned to different cohorts in light of corresponding TCM syndrome types and completed the 1-year-long cohort research. Before the start of this study, all researchers were trained to get familiar with the criteria of awarding scores, to improve the observation consistency of the researchers, and to ensure the reliability of the clinical research conclusions. The feasibility and accuracy of the entire process were overseen by two independent supervisors, who were responsible for inspection and confirmation of all records and reports of study data and case reports filled in correctly and completely, as well as the consistence with the original data. To ensure the follow-up visits of patients as scheduled, we will remind patients of their planned visit time via follow-up schedules, phone calls, or text messages.

### Study settings and participants

This study is still ongoing at Affiliated Hospital of Chengdu University of Traditional Chinese Medicine, and the identification of TCM syndrome types of the participants will be carried out by professional experts with TCM background. Regarding the data quality assurance of traditional Chinese medicine syndrome identification, the identification of traditional Chinese medicine syndrome types by participants will be carried out by two experts. In case of inconsistency, a third expert will be invited to join, and the final conclusion will be drawn after discussion among the three experts. The present study categorized the participants four TCM syndrome types: stagnant heat in gallbladder, damp heat in the spleen and stomach, deficiency and cold in lung qi, and deficiency and weak in spleen qi under the guide of *Otorhinolaryngology in Traditional Chinese Medicine* (Table 1) as Cohort 1, Cohort 2, Cohort 3, and Cohort 4. For eligible patients, investigators have detailed interpretation on purpose, specific content, and the designed methods on of how to complete the trial. Patients will be included in the study after the signature of informed consent.

**Table 1 Tab1:** Classification of TCM syndrome criteria

TCM syndrome types	Main symptoms	Accompanied symptoms	Tongue and pulse condition	Local examination
Stagnant heat in gallbladder	Nasal obstruction, decreasing sense of smell, bad headache, getting nasal purulence, in yellow or yellow green, in a large amount, or in odor	Whiny and irritability, mouth bitterness, throat drying, vertigo, tinnitus deafness, poor sleep	The tongue is red with yellow or greasy fur, and the pulse is rapid and profound or uneven and profound	Polyps are grayish or pale or dark red or easily bleeding and soft or tough
Damp heat in the spleen and stomach	Nasal obstruction, decreasing sense of smell, headache, runny nose, and yellow nasal discharge in a large amount	Distension and fullness in epigastric and abdominal areas, eating less, weakness and fatigue, viscous excrement	The tongue is red with yellow and greasy fur, and the pulse is rolling and rapid	Polyps are grayish or pale or dark red or easily bleeding and soft or tough
Deficiency and cold in lung qi	Nasal congestion or light or heavy, decreasing sense of smell, lightheadedness, runny nose which is white and sticky	Onset of sneezing, shortness of breath and fatigue, low faint voice, spontaneous sweating and chills from self	The tongue is pale with thin and white fur, and the pulse is weak and slow	Polyps are white or pale in color and soft
Deficiency and weak in spleen qi	Nasal congestion, decreasing sense of smell, lightheadedness, runny nose, runny or yellow white facies	Weakness and fatigue, eating less, abdominal distension, and loose stools	The tongue is fat with dentate marks, the fur is thin and white or white and greasy or little, and the pulse is wiry and weak	Polyps are white or pale in color and soft

After being included in the study, preoperative data of all participants will be collected, including general information, medical history, TCM syndromes, VAS score of subjective symptoms, Lund-Kennedy score of nasal endoscopy, and CT scan Lund-Mackay score of sinuses. Furthermore, follow-up visits were scheduled at weeks 2 and 4 and months 2, 3, 6, 9, and 12 after surgery, and the subjective symptom VAS score and the Lund-Kennedy score will be also obtained. After the 1-year follow-up, pathological sections of the patients who completed the trial will be obtained, and the infiltration of inflammatory cells will be analyzed under a 400-fold light microscope. Then, the recurrence rate and EOS count percentage of each TCM syndrome type will be applied, and a multiple regression model will be initially established to explore the correlation among postoperative recurrence of CRSwNP and TCM syndrome types and tissue inflammatory cell infiltration types. Finally, we will establish a predictive model for CRSwNP recurrence. The flow chart of the study is presented in Fig. 1. The SPIRIT schedule of enrollment, interventions, and assessments is presented in Fig. 2.

**Fig. 1 Fig1:**
[figure not shown]
Flow chart of the study

**Fig. 2 Fig2:**
[figure not shown]
SPIRIT schedule of enrollment, interventions, and assessments

If any participant discontinues follow-up visits, a serious adverse event (AE) occurs, any traditional Chinese medicine treatment is applied which might affect their prognosis during the follow-up period, or the investigator determined that it is inappropriate for the participant to continue the trial for safety reasons, this participant is withdrawn from the current research.

#### Inclusion criteria

Subjects are eligible to participate if they meet the following criteria: the patients are as follows:Meet the diagnostic criteria of European CRSwNP 2020 [1] and Chinese CRSwNP 2018 [2].Age between 12 and 75 years old (including 12 and 75 years old) and no gender limitAre ready to undergo FESSAre able to perform regular routine postoperative treatmentAre able to independently complete the questionnaire of this researchAre willing to participate in this trial and sign the informed consent form

#### Exclusion criteria

Subjects will be excluded if they meet any of the following criteria:Patients who have allergic fungal sinusitis, posterior nostril polyps, cysts, parasitic infections, autoimmune diseases, immunodeficiency diseases, severe systemic diseases, and mental illnessPatients who have a history of desensitization therapyPatients who have accepted antibiotics, glucocorticoids, and antihistamines treatments within 4 weeks before surgeryPregnancy or lactation

### Outcome measurements

Our researchers are responsible for follow-up of patients before surgery and at weeks 2 and 4 and months 2, 3, 6, 9, and 12 after surgery. After completing the 1-year follow-up, the recurrence rate will be calculated. Meanwhile, pathological sections of the patients who completed the trial will be analyzed, and the infiltration of inflammatory cells will be visualized under a 400-fold light microscope. All registered patients need to adhere to a 1-year follow-up plan before their data can be used for analysis.

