#### Primary outcome

The primary outcome of this study is to statistically analyze the recurrence rate 1 year after FESS and its correlation with traditional Chinese medicine syndrome types and eosinophil infiltration, in order to establish a predictive model for CRSwNP recurrence.

The definition of recurrence is that mucosal lesions (nasal polyps, mucus purulent discharge, and/or mucosal inflammation and edema) are seen under nasal endoscopy, the symptoms persist for 1 month without any alleviation, and maximum drug treatment is required [22].

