However, as a commonly introduced drug in clinic, glucocorticoid is one of the important pathogenic factors of nontraumatic femoral head necrosis [30]. Nasal glucocorticoids may cause side effects, namely epistaxis and perforation of the nasal septum, and the incidence of epistaxis has been reported to be as high as 20% in prolonged use of intranasal hormones over 1 year [31, 32]. However, hormones are an effective but helpless option to reduce the recurrence of CRSwNP and to control symptoms during recurrence.

Numerous studies have shown that the intervention of traditional Chinese medicine in the perioperative period can reduce the postoperative reaction of CRSwNP, minimize the reaction in the postoperative recovery stage, and help recurrence control [33–36]. We assume that the intervention of traditional Chinese medicine after surgery is necessary.

However, in clinical practice, it is very difficult to introduce the intervention of traditional Chinese medicine for every patient after surgery. The reason is mainly due to the economic burden that both patients and surgeons are not able to perform well. After FESS surgery, patients are required to perform postoperative endoscopic examination for about 1 year. Patients whose symptoms are not controlled or partially controlled need a longer period of drug treatment. If the intervention of traditional Chinese medicine is introduced at the same time, the patient is under an increased economic stress, thus leading to lower patient compliance. Meanwhile, as surgeons do not have an accurate prediction on which TCM syndrome type is likely or inevitably to relapse after surgery, they will also take into account the uncertainty in the ratio of the patient’s economic cost to benefit when prescribing traditional Chinese medicine. Consequently, the suggestions for Chinese medicine intervention treatment are discontinued.

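### The completers-only rule can discard recurrences already observed and selects the primary analysis set on events after surgery, some of which may be related to recurrence

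*Protocol article*

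**What the plan says.** Three statements in the protocol article define who is analysed.

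- Outcome measurements: "All registered patients need to adhere to a 1-year follow-up plan before their data can be used for analysis".
- Study settings and participants, in the paragraph after Fig. 2. The withdrawal triggers begin "If any participant discontinues follow-up visits, a serious adverse event (AE) occurs", continue with "any traditional Chinese medicine treatment is applied which might affect their prognosis during the follow-up period", and end with an investigator's judgement on safety grounds. The consequence is that "this participant is withdrawn from the current research".
- Histology is limited in the same way. Study settings and participants says "pathological sections of the patients who completed the trial will be obtained", and Outcome measurements repeats that "pathological sections of the patients who completed the trial will be analyzed".

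The primary outcome is to "statistically analyze the recurrence rate 1 year after FESS and its correlation with traditional Chinese medicine syndrome types and eosinophil infiltration", leading to a prediction model. Recurrence needs endoscopic lesions, symptoms lasting one month without relief, and a need for maximum drug treatment. Seven visits are scheduled, from 2 weeks to 12 months. The sample size section allows for 10% dropout. Nothing in the article keeps a recurrence that was documented before withdrawal.

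**The concern.** Nothing in the recurrence definition ties it to month 12, so it can be met at an earlier visit. A patient who meets it at month 3 and then stops attending, or starts TCM at month 6, has had an observed primary event, yet the rule removes that patient from numerator and denominator alike.

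The analysis set is thus selected on what happens after baseline, and at least two of the triggers may be related to the outcome. Loss to follow-up can depend on how well the patient is doing. TCM treatment is, on the authors' own account in the Discussion, able to "minimize the reaction in the postoperative recovery stage, and help recurrence control". Removing patients for receiving it also sits badly with Design overview and Safety assessments, which describe plain follow-up under real-world care.

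The recurrence rate and the predicted probabilities from the model are at stake, and possibly the association with syndrome type. Limiting histology to completers gives the eosinophil analysis the same selection.

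**Working it through.** **Inputs.** From Sample size calculation, the pilot recurrence was 11/26 = 42.3% (spleen qi), 2/32 = 6.25% (damp heat) and 0/13 = 0% (gallbladder). These add to 13/71 = 18.3%. Spleen qi against the other two types is 11/26 against 2/45 = 4.4%. The pilot gives no lung-qi figure. The article states no removal share by outcome, so every share below is an assumption. Applying the 10% dropout to the 200 planned patients gives 20 removed.

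**Formula.** With true risk p, and shares r1 of recurrent and r0 of non-recurrent patients removed:

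observed risk = p(1−r1) / [p(1−r1) + (1−p)(1−r0)]

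**Step 1: one group, only recurrent patients removed (r0 = 0), p = 0.423.**

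- r1 = 0.25: 0.317 / (0.317 + 0.577) = 35.5%. Loss in the group is 0.25 × 42.3% = 10.6%.
- r1 = 0.50: 0.2115 / (0.2115 + 0.577) = 26.8%. Loss in the group is 21.2%.

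**Step 2: limits for the overall rate, 20 of 200 removed.** A true 18.3% is 36.6 recurrences.

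- All 20 removed had recurred: (36.6 − 20) / 180 = 9.2%.
- None of the 20 had recurred: 36.6 / 180 = 20.3%.

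The same amount of loss can therefore move the rate either way.

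**Step 3: effect on the odds ratio.** The observed odds in a group are the true odds multiplied by (1−r1)/(1−r0). If that factor is the same in every syndrome group, it cancels from the odds ratio. It still shifts the model's intercept, and so its calibration. If it differs by syndrome, the odds ratio changes. The true odds ratio in the pilot is (11/15) / (2/43) = 15.8.

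| Assumed removal | Removed, of 71 | Spleen qi | Other two types | Odds ratio |
|---|---|---|---|---|
| None | 0% | 42.3% | 4.4% | 15.8 |
| 40% of recurrent, 5% of non-recurrent, both groups | 11.4% | 31.7% | 2.9% | 15.8 |
| 5% of recurrent, 20% of non-recurrent, both groups | 17.3% | 46.5% | 5.2% | 15.8 |
| 30% of recurrent spleen-qi patients, 5% of all others | 8.9% | 35.1% | 4.4% | 11.6 |
| 50% of recurrent spleen-qi patients, 5% of all others | 12.0% | 27.8% | 4.4% | 8.3 |

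Rows 2 and 3 shift the rates in opposite directions and leave the odds ratio alone. Rows 4 and 5 need removal to depend on recurrence and syndrome together. Removal of 10% at random would change none of these figures, and that is the only case in which recruiting 10% more patients is a sufficient answer.

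**The case against.** The strongest reply is that the bias may be small, or may run the other way.

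- The usual responses to recurrence are not withdrawal triggers. Maximum drug treatment is part of the recurrence definition, and Secondary outcomes foresees drug treatment and second surgery. A patient who recurs, is treated and keeps attending is analysed.
- The Discussion says that patients with incomplete control need longer drug treatment, which gives them a reason to stay in care, while recovered patients may drift away. If TCM prevents recurrence, removing its users may remove patients who would have stayed free of it.
- Reminders by schedule, phone and text should limit loss.
- Logistic regression is planned, and its odds ratio survives selection on recurrence alone.
- Handling of missing data normally belongs in the analysis plan, which is not shown.

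The first four stand, and they rule out some stronger readings. A reader might infer that the recurrence rate must be biased downward; the documents support either direction. A reader might infer that TCM is prescribed by syndrome; the Discussion says instead that surgeons cannot predict which syndrome will relapse and that, partly for cost, TCM advice is dropped. A reader might take serious adverse events to be linked to recurrence; nothing in the article says so. The 40% recurrence rate in the Background is an 18-month literature figure and is not the planning rate.

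The last reply does not stand. The article states the exclusion rule itself, so this is more than a detail left to another document.

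**Conclusion.** The concern holds as a defect in a stated rule. Followed as written, the plan can discard primary events that were observed, and it conditions the analysis set on post-baseline events, of which TCM use and loss to follow-up may be related to recurrence. The 1-year rate and the calibration of the prediction model can be biased. A distorted odds ratio is plausible but not shown.

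The size is conditional on assumed removal shares. In the scenarios above, an observed spleen-qi risk between about 27% and 47% is compatible with a true 42.3%, and losing 20 of 200 leaves an overall 18.3% anywhere between 9.2% and 20.3%. I am confident about the rule and its consequence, but not about direction.

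**What to change.** Delete the completers-only rule and replace it with the following.

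1. Include all enrolled, operated participants in the primary analysis.
2. Count any recurrence meeting the protocol's definition up to 12 months or before exit, whatever happens afterwards.
3. For those who leave recurrence-free, use a time-to-recurrence analysis with censoring, or multiple imputation from baseline data and the last VAS and Lund-Kennedy scores.
4. Record TCM use, with its date, as an intercurrent event and keep the data. Add a sensitivity analysis that censors at TCM start, which also serves an interest in recurrence without TCM. Do not count TCM start as a recurrence, since that would contradict the protocol's own definition.
5. Add best-case and worst-case sensitivity analyses for those with unknown 12-month status.
6. Read eosinophils in all operated participants whose surgical sections are available. The article does not say whether sections from non-completers are kept, so this needs checking.

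These changes concern data handling only and alter no treatment. The cost is new wording, some extra analysis and additional slide reading. Recruitment began in January 2021, so data not collected after earlier withdrawals cannot be recovered; the number affected should be reported by syndrome type and by recurrence status at exit.
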